### Trial outcome assessment

The predefined outcomes will be recorded in an electronic case record form developed by the HRBCRFG.

### Evaluation of perioperative myocardial infarction

Evaluation of pre- and post-operative electrocardiograms and troponin levels for evidence of perioperative silent myocardial infarction will be undertaken in batches by the trial cardiologist, [name]. [name] will be blinded to the trial allocation of each participant.

### Evaluation of other outcomes

The development of the remaining outcomes will be determined by a trial research nurse in the Dublin site and by research fellows in the remaining three non-Dublin sites. The individuals assessing these primary and secondary outcomes will be blinded to the trial allocation of the patients, in order to minimise potential sources of bias.

### Evaluation of acceptability and barriers to implementation

Whilst RIPC is simple to induce and inexpensive, it does add to the burden of clinical staff in advance of major vascular surgery. Perceptions that the intervention is onerous will significantly impede adoption into routine practice should a clinical benefit be demonstrated. It may also significantly hinder recruitment in any phase 3 trial, as reluctance to complete the preconditioning protocol may result in numerous protocol breaches in the intervention arm. For patients, particularly those undergoing regional anaesthesia rather than general, the intervention may be burdensome and uncomfortable, again negatively impacting upon likely adoption into routine practice.

In order to explore these potential issues in advance of any full-scale trial, the feasibility trial will include a qualitative evaluation of acceptability to both patients and clinical staff together with a qualitative evaluation of any perceived barriers to implementation. These insights may be of value in the subsequent design of a full-scale trial and may help adoption of RIPC in routine practice should the intervention prove clinically and economically-efficacious.

Healthcare professionals at participating practices will be asked to complete a self-administered questionnaire at the end of the study period. The questionnaire will elicit data on profession and practice details, their perceived experience of trial involvement, and open-ended questions to elicit information regarding attitudes to trial involvement, willingness to recruit participants, difficulties that arose during the trial and potential barriers to further research or routine clinical use of the trial intervention.

A convenience sample of 40 patients (10 from each site) will be contacted following their surgery to conduct a brief interview. This will again involve the use of open-ended questions in order to elicit information regarding patients’ attitudes towards the intervention and perceived barriers to implementation.

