### Study setting

Patients undergoing scheduled major vascular surgery will be screened for eligibility in five vascular surgery units in the Republic of Ireland. Patients will receive routine perioperative care according to the current standard of care. During the study period, patients will be discharged home or to continuing care facilities within the geographic area.

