### Intervention

The intervention being tested is a simple intervention that can be undertaken using existing equipment. Immediately before the start of the operation, patients randomised to the RIPC arm will have a standard, CE-approved tourniquet cuff placed around one upper limb. It will then be inflated to a pressure of 200 mmHg for 5 minutes. For patients with a systolic blood pressure >185 mmHg, the cuff will be inflated to at least 15 mmHg above the patient’s systolic blood pressure. The cuff will then be deflated and the arm allowed to reperfuse for 5 minutes. This will be repeated so that each patient receives a total of four ischaemia-reperfusion cycles. There is no sham intervention for those in the control arm.

Previous trials of RIPC in cardiac surgery and percutaneous coronary interventions have generally used the arm as the source of the RIPC stimulus. Four previous trials of RIPC in major vascular surgery (Table 1) used the patients’ legs to generate the stimulus. In these trials, four patients in the RIPC arm developed post-operative critical lower limb ischaemia requiring intervention. The presence of known peripheral arterial disease also precluded the enrolment of about 20% of otherwise eligible patients. Given the success of upper limb RIPC in the cardiac and percutaneous coronary intervention (PCI) trials, the upper limb has been selected as the source for the RIPC stimulus in Preconditioning SAVES. In common with the ERICCA trialists [27], four cycles has been chosen in order to maximise the RIPC stimulus obtained and counteract three potential confounding issues: (i) the lower skeletal muscle bulk in the arm compared to the leg, (ii) the potential resistance to RIPC in aging and diabetic patients and (iii) the effect of variable volatile anaesthetic use.

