The planned patient cohort for this feasibility trial is very similar to that reported above. Moreover, analysis of preliminary data from 40 patients randomised at University Hospital Limerick found that 19/40 patients developed a troponin-positive event (47.5%). Assuming a 40% incidence of troponin-positive events, 166 patients would be required in each arm to demonstrate a reduction to 25% (alpha 0.05, beta 0.8). To account for dropouts and losses to follow-up, we plan to recruit 200 patients to each arm of the trial. This sample will also provide robust data regarding the likely incidence of the proposed composite primary efficacy endpoint for a phase 3 trial. At 25% of the proposed full trial recruitment, the investigators feel it is sufficiently large to allow adequate testing of trial procedures and compliance at multiple sites in line with objective (i) above.

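### The patient interviews on cuff burden use a convenience sample with no stated selection by arm or anaesthesia type, and 10 per site gives 40 only with four sites, not the five stated

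*Protocol article*

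**What the plan says.** The Protocol article, under Evaluation of acceptability and barriers to implementation, gives the reason for the qualitative work: "For patients, particularly those undergoing regional anaesthesia rather than general, the intervention may be burdensome and uncomfortable". The patient component is then fixed: "A convenience sample of 40 patients (10 from each site) will be contacted following their surgery to conduct a brief interview". Its stated subject is patients' "attitudes towards the intervention and perceived barriers to implementation". The section names no arm, anaesthesia type or completion status as a basis for selection.

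Other sections bear on this:

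- Intervention: "There is no sham intervention for those in the control arm".
- Sample size: "we plan to recruit 200 patients to each arm of the trial", so allocation is 1:1.
- Perioperative data: anaesthetic induction and maintenance are recorded for every patient.
- Qualitative data analysis: half the interviews are coded first to find common codes per respondent group, and the rest are added one by one to monitor saturation. The groups are not defined.
- Study setting: patients "will be screened for eligibility in five vascular surgery units in the Republic of Ireland". The Abstract also says five centres.
- Evaluation of other outcomes: outcome assessors are described for one Dublin site and three others, which makes four.
- Informed consent and ethical approval: approvals are listed for six hospitals.

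**The concern.** The sampling method does not fit the question it is meant to answer. The question is how the cuff feels, above all to patients who are not under general anaesthesia. A convenience sample takes whoever is easiest to reach. Nothing in it ensures that patients who had the cuff under regional anaesthesia, or who stopped before the fourth cycle, are among the 40. A control can speak about consent, participation and perceived barriers, but cannot report the discomfort of a cuff that was never applied.

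Acceptability to patients and staff is a stated purpose in the Abstract. Uncertainty about it is one of the reasons given for running the feasibility study, and the Discussion lists the qualitative evaluation as a strength. If few interviewees can describe the burden, the phase 3 design gets little information on the point this component was set up to examine. Monitoring saturation does not cure this, because it shows only that the people who were interviewed have stopped adding new themes.

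The site arithmetic is a second, independent defect. As written, the interview plan cannot be carried out at five sites with 10 each and still total 40.

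**Working it through.** **1. The plan's own figure.** Total = sites × 10.

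- Four sites: 4 × 10 = 40, which reproduces the stated total and agrees with the four sites implied under Evaluation of other outcomes.
- Five sites (Abstract, Study setting): 5 × 10 = 50. Keeping 40 would mean 40 / 5 = 8 per site, or leaving one site out.
- Six hospitals (ethics approvals): 6 × 10 = 60.

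**2. Interviewees without cuff experience, if the draw ignores arm.** Inputs: 400 patients, 200 of them controls, 40 interviewed. The condition is an assumption, since the document does not state the arm. Treating the draw as random without replacement (hypergeometric):

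- Mean = 40 × 200/400 = 20.
- SD = √(40 × 0.5 × 0.5 × 360/399) = √9.02 = 3.0.
- The 2.5% and 97.5% points are 14 and 26.

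So about 20 of 40 would never have had the cuff. The mean needs only that selection be unrelated to arm. The range also needs the convenience draw to behave like a random one.

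**3. Interviewees with both cuff and regional anaesthesia.** The share under regional anaesthesia, r, is not in the document and is assumed here to be the same in both arms. The expected number is 40 × 0.5 × r if arm is ignored and 40 × r if only RIPC patients are interviewed. The chance of having none, if arm is ignored, is (1 − 0.5r)^40 by the binomial approximation.

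| Assumed r | Arm ignored | RIPC only | Chance of none (arm ignored) |
|---|---|---|---|
| 10% | 2 | 4 | 13% |
| 20% | 4 | 8 | 1.5% |
| 30% | 6 | 12 | 0.2% |
| 50% | 10 | 20 | below 0.01% |

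Restricting to the RIPC arm doubles the expected number with no extra interviews. A quota would fix the number by design, so that it would no longer depend on r.

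**4. The part that needs no assumption.** Even if the 40 were all RIPC patients, the stated method would still not target regional anaesthesia. At r = 10% it would yield about 4 such patients by chance.

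**The case against.** The strongest reply is that the arm is simply not stated. Asking about attitudes to the intervention is quite compatible with interviewing only patients who received it, and a journal article may leave the sampling frame to the full protocol. This stands. A reader might infer that the sample is drawn from all trial patients and that half the interviewees never had the cuff; the text does not say so, and the 20 of 40 is conditional. The reply does not cover the choice of convenience sampling, which the article does state and which does not match the concern it states about regional anaesthesia.

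The figures are also open to challenge. A convenience sample is not random, so 14 to 26 is only indicative, and 2 to 6 rests on an assumed share. Both points stand.

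Two further inferences are tempting and unsupported. One is that the transcripts would be largely uninformative: even with arm ignored, about half would come from RIPC patients, and controls can discuss barriers and participation. The other is that RIPC would look more acceptable than it is: the document does not show the direction of any bias, and people who never felt the cuff might be more wary of it.

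It can also be said that this is a brief exploratory component that feeds no trial endpoint, that staff questionnaires supply other evidence on burden, and that the coding safeguards are sound. This limits the importance of the point, but neither staff reports nor careful coding supplies the experience of patients who were not interviewed.

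Finally, the Weaknesses section describes minimal trial staffing, so separate interviewers may be hard to find. But an interview about the cuff reveals allocation whichever way patients are chosen, so the plan as written already needs someone other than the blinded assessor.

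**Conclusion.** The concern holds in a limited form. The plan states a convenience sample for a question about cuff burden, names patients under regional anaesthesia as the main worry, and states no selection by arm or anaesthesia type. That mismatch is on the page and needs no assumption.

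Its size is conditional. About 20 of 40 interviewees (roughly 14 to 26) would lack cuff experience if patients are drawn regardless of arm in a random-like way, and about 2 to 6 would have had both cuff and regional anaesthesia if 10 to 30% receive it. The document confirms neither condition.

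The site mismatch is real and unconditional: 40 at 10 per site means four sites, against five in the Abstract and Study setting. It is part of a wider inconsistency in the number of sites and says nothing about arm or anaesthesia.

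The change is worth making because acceptability is a stated purpose and a better method needs no more interviews. The primary endpoint and its analysis are unaffected.

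**What to change.** - Keep about 40 interviews, but state that they are selected purposively from patients allocated to RIPC.
- Make sure that patients under regional anaesthesia and patients who did not complete all four cycles are included, for example by minimum quotas. The anaesthetic data already being recorded can help to identify the first group.
- If control views on participation are wanted, take them as a separate, separately reported set.
- Reconcile the number of sites across the Abstract, Study setting, ethics approvals, Evaluation of other outcomes and the interview plan, then set the per-site count to match. Eight per site would be right only if five is confirmed.
- State that interviewers are not the blinded outcome assessors.

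The cost is a change of wording and slightly more effort to fill the quotas. Keeping interviewers apart from blinded assessors is a real constraint with minimal staffing, but the present plan already carries it.

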### Sample size

Currently, the projected sample size for a full phase 3 trial using the composite clinical endpoint mentioned above is 1,500 patients in total. This would provide sufficient power to detect a reduction in the proportion of patients sustaining the endpoint from 15% to 10% (alpha 0.05, beta 0.8). The assumed 15% figure in the control arm is based upon data from a sample of only 40 patients randomised at University Hospital Limerick. Before proceeding with a full-scale trial, and in accordance with the MRC framework for the evaluation of complex interventions, it would be preferable to (i) explore the feasibility of randomising a significant number of surgical patients in the Irish healthcare system context, (ii) undertake further work using a surrogate marker of efficacy to more robustly evaluate the apparent protective effect of RIPC in major vascular patients, (iii) use such a surrogate marker to evaluate the likely effect size of RIPC, and (iv) confirm that arm-induced RIPC is protective in major vascular patients.

In order to fully evaluate objectives (ii) to (iv) above, the feasibility trial design utilises troponin-positive events as the primary outcome. The sample size calculation for the pilot trial is based upon recently published data regarding post-operative troponin-positive events following major vascular surgery. In a cohort of 337 patients undergoing a mix of major vascular procedures (open and endovascular aneurysm repair, carotid endarterectomy or surgical lower limb revascularisation), 135 (40%) developed a post-operative troponin level in excess of the upper limit of normal. At one year post-surgery, patients with a troponin positive event, that is, those with a level in excess of the upper limit of normal, were more likely to have died [28].

The planned patient cohort for this feasibility trial is very similar to that reported above. Moreover, analysis of preliminary data from 40 patients randomised at University Hospital Limerick found that 19/40 patients developed a troponin-positive event (47.5%). Assuming a 40% incidence of troponin-positive events, 166 patients would be required in each arm to demonstrate a reduction to 25% (alpha 0.05, beta 0.8). To account for dropouts and losses to follow-up, we plan to recruit 200 patients to each arm of the trial. This sample will also provide robust data regarding the likely incidence of the proposed composite primary efficacy endpoint for a phase 3 trial. At 25% of the proposed full trial recruitment, the investigators feel it is sufficiently large to allow adequate testing of trial procedures and compliance at multiple sites in line with objective (i) above.

### Statistical analysis plan

The statistical analysis plan has been developed in conjunction with the HRBCRF Galway. The statisticians will be blinded to the trial allocation for all analyses, with the two trial arms being labelled A and B.

### Interim analysis

An interim analysis will be undertaken once 200 patients have been recruited and 30-day follow-up accrued. This analysis will be undertaken by [name], HRBCRF Galway. The interim analysis will be reviewed by the Data Monitoring Committee ([name], [name] [name], and [name]) and used to provide a recommendation to the Trial Management Committee as to whether the adaptive clauses in the trial design should be invoked.

### Final analysis

Once the trial has closed, a final analysis of the data will be conducted by [name], the trial biostatistician. The trial arms will be labelled A and B, to maintain blinding. Baseline characteristics will be compared between the trial arms to evaluate the efficacy of randomisation. The proportions of patients with troponin positive events, components of the composite clinical outcome, primary safety endpoints, troponin levels, unplanned critical care admission and other post-operative complications will be compared between the trial arms. Hospital stay and intensive care unit stay will also be compared between the two trial arms. One-year survival and cardiac- and cerebral-event free survival will be compared. These results will all be presented in the final trial report.

### Subgroup analyses

Experimental data suggest that the protective effect of RIPC may be attenuated in diabetic patients. This trial provides an opportunity to evaluate the relationship between RIPC and diabetes in clinical practice. There will be two components to this analysis. In the diabetic subgroup, the proportion of patients suffering a troponin-positive event will be compared between those patients who receive RIPC and patients who are controls. In addition, the proportion of patients suffering a troponin-positive event will be compared between diabetic RIPC patients and non-diabetic RIPC patients, in order to determine whether the effect size of RIPC differs significantly in diabetic patients. These data will inform subsequent design of a phase 3 trial, should it appear justified.

There have also been suggestions that RIPC is attenuated in older patients. Again, this trial provides an opportunity to investigate this potential relationship further. Proportions of the patients sustaining a troponin-positive event will be compared between patients aged ≥80 years at randomisation and patients aged <80 years at randomisation. The proportion with a troponin positive event will also be compared between RIPC and control patients in the ≥80 subgroup. A between group analysis will compare the proportions of troponin positive events between RIPC patients in the ≥80 and <80 groups. These data will again inform subsequent design of a phase 3 trial, should it appear justified.

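### The RIPC-only comparisons planned for diabetes and for age cannot show whether the RIPC effect differs between subgroups, because without controls they mix baseline risk with treatment effect

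*Protocol article*

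**What the plan says.** The protocol article, under the heading on subgroup analyses, lists five comparisons of the troponin-positive proportion.

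For diabetes it fixes the number: "There will be two components to this analysis".
- The first is between arms, with the control arm as comparator (the quote stops just before that last word): "In the diabetic subgroup, the proportion of patients suffering a troponin-positive event will be compared between those patients who receive RIPC and patients who are".
- The second lies wholly inside the RIPC arm. Here the plan wants proportions "compared between diabetic RIPC patients and non-diabetic RIPC patients, in order to determine whether the effect size of RIPC differs significantly in diabetic patients".

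For age the motive is given as "There have also been suggestions that RIPC is attenuated in older patients". Three comparisons follow.
- One is by age without reference to arm: "compared between patients aged ≥80 years at randomisation and patients aged <80 years at randomisation".
- One is between arms: "The proportion with a troponin positive event will also be compared between RIPC and control patients in the ≥80 subgroup".
- One is inside the RIPC arm: "A between group analysis will compare the proportions of troponin positive events between RIPC patients in the ≥80 and <80 groups".

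Both paragraphs end by saying that the results will feed into the design of a phase 3 trial, if one is justified. The health economics section plans to look at heterogeneity by age and diabetes, but only for economic treatment effects.

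**The concern.** The effect of RIPC in a subgroup is the contrast of RIPC with control in that subgroup. Whether the effect differs between subgroups is a contrast of two such contrasts, so it needs four cells: RIPC and control, each at both subgroup levels. The comparison that the protocol assigns to this question uses two cells, both treated. If diabetics have raised troponin more often for reasons unrelated to RIPC, the comparison will tend to show a difference even when RIPC works equally well in them. If their baseline risk is lower, it can hide a real loss of effect.

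At stake is what the pilot tells the designers of the phase 3 trial. They could conclude that diabetics or older patients respond less to RIPC when those patients are only at higher risk, or be reassured when the effect is absent.

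**Working it through.** **What the RIPC-only contrast measures.** Write R and C for RIPC and control, D and N for diabetic and non-diabetic, and p for the troponin-positive risk. Then

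p(RD) − p(RN) = [p(CD) − p(CN)] + {[p(RD) − p(CD)] − [p(RN) − p(CN)]}.

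The first bracket is the baseline-risk gap and the second is the difference in treatment effect. On the ratio scale, p(RD)/p(RN) = [p(CD)/p(CN)] × [RR(D)/RR(N)]. The left side alone does not identify the last term unless the control risks are equal. The same holds for age.

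**The plan's own figures.** The sample size section states: "Assuming a 40% incidence of troponin-positive events, 166 patients would be required in each arm to demonstrate a reduction to 25% (alpha 0.05, beta 0.8"). Reading beta 0.8 as 80% power, with a two-sided test, the two-proportion formula gives 152 per arm without continuity correction and 165 with it, against 166 stated. The corrected formula also gives 726 for 15% v 10%, as the rationale section states. The planning figures therefore reproduce. They supply the overall control risk (40%), the risk ratio (0.25/0.40 = 0.625) and, after the dropout allowance, 200 patients per arm.

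**Assumed inputs.** The documents give no share of diabetics, no share aged 80 or over, and no subgroup risks. I assume 25% diabetic (50 v 150 in the RIPC arm) and the same risk ratio of 0.625 in both groups, so there is no effect modification on that scale. Control risks are chosen to average 40%; for example 0.25 × 52% + 0.75 × 36% = 40%.

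**False signal, one case by hand.** For control risks of 52% v 36%:
- RIPC-arm risks are 0.52 × 0.625 = 32.5% and 0.36 × 0.625 = 22.5%, a gap of 10 points.
- The pooled risk is 25%, so the null standard error is √[0.25 × 0.75 × (1/50 + 1/150)] = 0.0707, and significance needs a gap of 1.96 × 0.0707 = 0.1386.
- The actual standard error is √[0.325 × 0.675/50 + 0.225 × 0.775/150] = 0.0745.
- The probability of significance is about Φ[(0.10 − 0.1386)/0.0745] = Φ(−0.52) ≈ 0.30. Exact binomial enumeration gives 0.307.

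**Exact results for the two-sided pooled z-test, 50 v 150.**

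| Control risk, diabetic v non-diabetic | RIPC risk | Truth | RIPC-only test significant |
|---|---|---|---|
| 44% v 38.7% | 27.5% v 24.2% | same risk ratio | 8% |
| 52% v 36% | 32.5% v 22.5% | same risk ratio | 31% |
| 61% v 33% | 38.1% v 20.6% | same risk ratio | 69% |
| 52% v 36% | 52% v 36% | RIPC inert in both | 52% |
| 25% v 45% | 25% v 25% | no effect in diabetics, full effect in the rest | 5% |

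**Range over the assumptions.** With 200 per arm, diabetic shares of 10% to 40% and diabetic control risks of 45% to 60% (40% overall), the false-signal rate by normal approximation runs from 7% to 91% under a common risk ratio, and from 8% to 99% under a common odds ratio of 0.50. If control risks are equal, it is 5%.

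**The four-cell alternative.** With a common risk ratio and control risks of 52% v 36%, an interaction test rejects in about 5% of simulated trials. In the last row of the table it rejects in about 34% (log risk ratio) to 40% (log odds ratio), where the RIPC-only test finds nothing. Its power is low in general. For complete loss of effect in the subgroup, with a 40% control risk in both groups and 200 per arm, it is about 17%, 27%, 33% and 37% for subgroup shares of 10%, 20%, 30% and 40%.

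**The case against.** Four points can be made for the plan.

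1. *Most of the listed comparisons are not RIPC-only.* This stands. A reader might infer that the whole subgroup section compares treated patients with treated patients. In fact two of the five comparisons do so, and two are sound randomised contrasts of RIPC with control. The fifth, by age alone, is never claimed to measure effect modification and is no error. But an effect estimated in diabetics, with no counterpart in non-diabetics, does not show that the two effects differ.

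2. *The age paragraph does not promise a test of effect size.* This also stands. That purpose is written only for diabetes. For age it is implied by the attenuation hypothesis, so the age half of the point is weaker.

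3. *The sizes are hypothetical.* They are, and the case of missed attenuation needs diabetics to have a lower control risk than non-diabetics, which nothing in the document suggests. A reader might infer that attenuation would be reported whenever a subgroup has a higher baseline risk. The figures do not support that: with a small gap (44% v 38.7%) the rate is about 8%. The flaw in the contrast itself does not depend on these inputs.

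4. *The statistical analysis plan may set out an interaction test.* It may, but the protocol does not leave the method open. It names a contrast and gives it a purpose that the contrast cannot serve.

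**Conclusion.** The rule is wrong as written. For diabetes, the protocol assigns a RIPC-only comparison to a question about differing treatment effects. For age, it plans the same kind of comparison with that question implied. The contrast would answer the question only if control risks were equal across the subgroups, which the document does not claim.

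The size depends on subgroup shares and risks that the documents do not give. Under the assumptions above, a false signal arises in about 8%, 31% or 69% of trials as the baseline gap widens, and complete attenuation can pass unseen.

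This should be fixed, but its reach is limited. A reader might infer that the trial's main result is compromised. It is not: the primary comparison, the sample size, the safety endpoint and the interim decision do not use these contrasts. The harm is misleading subgroup evidence for phase 3 planning.

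**What to change.** For troponin-positive events, base the effect-modification question on two interaction estimates, arm by diabetes and arm by age (80 or over v under 80), each using all four cells. Give each as a ratio of treatment effects with its 95% confidence interval, and state the scale (risk ratio or odds ratio) in advance. Report RIPC versus control, with intervals, at every level: diabetic, non-diabetic, 80 or over, and under 80. Label these analyses exploratory and say that power to detect an interaction is low. Drop the two RIPC-only contrasts, or keep them relabelled as descriptive and remove the statement that one of them determines whether the effect size differs.

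The cost is wording in the protocol and the analysis plan. Diabetes and date of birth are already in the baseline data, so nothing new has to be collected. The drawback is that the interaction estimates will be imprecise, so the subgroup question will probably stay open after this trial.
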